## Methods

### Study design

This type 2 hybrid effectiveness-implementation study uses a convergent mixed-methods approach, as previously described in other similar studies conducted by our group
^
21,
22
^. SMC with SPAQ and DP will be implemented in five monthly cycles between June 2022 and October 2022 in five districts of Karamoja. Over 85,795 children aged 3–59 months, in Kotido and Moroto for phase 1 of the study, will continue to receive SMC in phase 2, and in addition, 60,000 children in three districts (Nabilatuk, Amudat, and Nakapiripirit) will receive SMC for the first time. The research will involve the following components: 1) Conducting a cluster randomized controlled trial (cRCT) using passive surveillance to establish confirmed malaria cases among participating children; 2) conducting a prospective chemoprevention efficacy cohort study to determine whether SPAQ and/or DP provides 28 days of protection from infection, and whether drug concentrations and/or resistance influence the duration of protection; 3) conducting a resistance markers study in children aged 3–59 months in the three research districts plus the two standard intervention districts to describe changes in resistance marker prevalence over time; and 4) conduct a process evaluation of the SMC implementation looking at cost and process outcomes
^
6
^.

### Study setting

The study will be conducted in five districts of Karamoja region as shown in
Figure 1 below. The cRCT will be conducted in Amudat. The chemoprevention component will be conducted in Nakapiripirit because SMC has not been previously implemented in this location therefore drug resistance selection pressure from a previous year of SMC implementation will be avoided or minimized and malaria rates are expected to be higher allowing for a greater detection of breakthrough infections. The resistance markers component will be conducted in all five districts inclusive of Nabilatuk, Kotido and Moroto, as well as the process evaluation for assessment of the SMC implementation model.

**Figure 1. f1:**
[figure not shown]
Area of implementation of Year 2 SMC in Uganda.

### Population

Eligible participants for receiving SMC will be male or female children with no fever, aged 3–59 months for any of the SMC cycles, staying in the districts of Kotido, Moroto and Nabilatuk districts (where delivery is continuing from Phase 1 and where coverage surveys will be conducted in Phase 2), and randomly-selected areas in Amudat and Nakapiripirit.

Additionally, other key stakeholders who will be sampled include health workers participating in implementing SMC, health officials at different levels of the health system, community leaders, and caregivers of children below ten years of age, (see
Table 1 for estimated population sizes).

**Table 1. T1:** Sample sizes for each objective.

Objective	Study population	Estimated sample size
1	cRCT: Sample of eligible children in Amudat district of age 3–59 months, resident in the study area for at least a month, planned for DP and SPAQ	4,270
2a	Chemoprevention efficacy cohort study – children under 3–59 months for SPAQ and 6-59 months for DP	1,250
2b	Safety of DP in 3–6 month old children through pharmacometrics to low dose DP.	30
3	Resistance Marker study – children under 5	1,500
4	Assessment of the SMC implementation model, deciding the process, costing and acceptability outcomes of the intervention	144
**Total number of participants:**		**7,194**

### Recruitment and data collection

**
*cRCT component.*
** In the control arm, one eligible child will be recruited at random in each household of which, researchers from selected communities will have randomly selected. Informed consent will be obtained from caregivers, then children will be enrolled and their eligibility confirmed using a short baseline questionnaire to collect individual data on each child.

For the intervention arms, VHTs will be followed by a researcher as they administer SMC. Households in selected communities will be randomly sampled from those visited by the VHTs. Before SMC is initiated, one eligible child will be recruited, and a short baseline questionnaire will be administered to collect individual data and to confirm their eligibility. Informed consent will be obtained from caregivers and then a questionnaire used for collecting individual child data, to which all household questions from the end-of-round survey will be added (e.g. on household wealth, language, migration status, education and level of literacy of caregivers and heads-of-household, etc.), and to determine their eligibility. Blood samples will be taken for haemoglobin concentration measurement using a Hemocue machine.

The primary endpoint will be recorded with passive surveillance conducted by study clinicians in intervention and control areas throughout the five-month study period.

Children recruited into the study presenting at clinics or to VHTs will be identified using information on their SMC record cards, and data on clinic visits including suspected malaria cases and results of RDTs will be matched to baseline questionnaire data to build a database for analysis. Date of clinic attendance and confirmation of malaria cases using rapid diagnostic tests will be recorded to allow for calculation of follow-up time and time to malaria events for fitting of Cox proportional hazards regression model. This will be facilitated through matching of codes on children's SMC cards with records of the same codes in clinic logbooks.

**
*Chemoprevention efficacy cohort study.*
** Children will be screened at the community level by research assistants with the help of VHTs and referred to a designated study clinic for further assessment and non-randomized recruitment. At the study clinic, study clinicians will confirm eligibility criteria through conversation with the caretaker and obtain informed consent. Enrolled children will receive SMC via directly observed therapy (DOT) over the first three days and will have malaria thick smears and dry blood spots (DBS) taken at day 0, 2, 7, 14, 21 and 28 throughout and after administering a single cycle of SPAQ or DP. In addition, the study clinician will assess if the child received other treatment or experienced any problem during all the scheduled sample collection days (Day 0, 7, 14, 21, 28) as well as bed net usage. Caregivers and guardians will also be reminded at each visit to seek care at a health facility or from a community health worker if the child becomes febrile. Children who become febrile and are confirmed on HPR2-pLDH RDT between day 0 and day 28 will have an additional DBS taken and then treated using standard guidelines. All DBS samples will be processed for all of the SMC drugs on days 7 and for sulfadoxine, amodiaquine and piperaquine for day 28. Individual surveys on day 28 after the final DBS is taken will be conducted to determine if the child received other treatment or experienced illness over the past month of study implementation. On day 0 and day 28, they will also be processed to ascertain low density parasitaemia estimates through quantitative polymerase chain reaction (qPCR).
Figure 2 below depicts the planned sample collection time points and subsequent sample processing sequence). We aim to recruit participants from Nakapiripit, one of the two research districts.

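### cRCT recruitment depends on a VHT visit in the SMC arms only, which risks selection bias and shifts the estimand in SMC versus control

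*Protocol article*

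**What the plan says.** All of this is in the protocol article, Recruitment and data collection, cRCT component.

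- **Control arm, households.** "one eligible child will be recruited at random in each household of which, researchers from selected communities will have randomly selected". The list or area from which these households are drawn is not stated, and no VHT visit is involved.
- **SMC arms, households.** "For the intervention arms, VHTs will be followed by a researcher as they administer SMC". Then: "Households in selected communities will be randomly sampled from those visited by the VHTs".
- **SMC arms, timing.** "Before SMC is initiated, one eligible child will be recruited", so the child enters before the drug is given.
- **Baseline data, control.** Children are enrolled and "their eligibility confirmed using a short baseline questionnaire to collect individual data on each child".
- **Baseline data, SMC arms.** The same kind of short questionnaire is used, then a further one "to which all household questions from the end-of-round survey will be added", with wealth, migration and education among the examples. The paragraph ends: "Blood samples will be taken for haemoglobin concentration measurement using a Hemocue machine". The control paragraph mentions neither the household items nor haemoglobin.

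Three other sections bear on the point. Aims and objectives gives the first objective as the effectiveness of SMC in reducing malaria incidence. The Introduction describes door-to-door delivery and calls coverage in the 2021 phase high, without a percentage and for two districts. Study setting places the cRCT in Amudat, which Study design lists among the districts receiving SMC for the first time.

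**The concern.** Whether a VHT visits a household is decided after the cluster is allocated, and only in clusters that receive SMC. A household that the VHT misses cannot enter the SMC sample, while a similar household in a control cluster can. Randomising clusters balances the populations of those clusters. It does not balance samples drawn from them by different rules.

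Two separate things are at stake. The first is selection bias: if missed households differ in malaria risk from visited ones, the two samples differ in baseline risk. The second is the estimand: effectiveness of a delivered programme includes its failures of reach, and a visited-only frame takes those failures out of the SMC arms even when baseline risks are equal.

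The difference in baseline data adds to this but does not cause it. If control children have no household items or haemoglobin, an imbalance in these cannot be shown or adjusted for.

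**Working it through.** **Plan's own figures.** The article gives no coverage figure for Amudat, so there is nothing on this point to reproduce. Table 1 gives 4,270 children for the cRCT, and its total adds up (4,270 + 1,250 + 30 + 1,500 + 144 = 7,194). Neither number enters the calculation.

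**Inputs, all assumed.**
- c: among households that the control procedure could recruit, the share that a VHT would visit.
- k: malaria rate without SMC in unvisited households, relative to visited ones.
- r: true rate ratio, SMC versus none, in visited households.
- Unvisited households are taken to receive no SMC at all.

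**Formulas.** Set the rate without SMC in visited households to 1. The control sample then has average rate D = c + (1 − c)k.
- Ratio that the plan estimates: r / D.
- Ratio with one frame of all households in every arm: (rc + (1 − c)k) / D.
- Difference, second minus first: (1 − c)(k − r) / D.

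**Step 1: no true effect (r = 1).** With one common frame the ratio is 1.00. As written it is 1 / D:

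| c | k = 0.5 | k = 1 | k = 1.5 | k = 2 |
|---|---|---|---|---|
| 0.98 | 1.010 | 1.000 | 0.990 | 0.980 |
| 0.95 | 1.026 | 1.000 | 0.976 | 0.952 |
| 0.90 | 1.053 | 1.000 | 0.952 | 0.909 |
| 0.80 | 1.111 | 1.000 | 0.909 | 0.833 |

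For example, c = 0.90 and k = 2 give D = 0.90 + 0.20 = 1.10 and 1 / 1.10 = 0.909.

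**Step 2: a true effect (r = 0.50).** Each cell shows the ratio as planned, then with all households:

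| c | k = 0.5 | k = 1 | k = 1.5 | k = 2 |
|---|---|---|---|---|
| 0.95 | 0.513 / 0.513 | 0.500 / 0.525 | 0.488 / 0.537 | 0.476 / 0.548 |
| 0.90 | 0.526 / 0.526 | 0.500 / 0.550 | 0.476 / 0.571 | 0.455 / 0.591 |
| 0.80 | 0.556 / 0.556 | 0.500 / 0.600 | 0.455 / 0.636 | 0.417 / 0.667 |

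For example, c = 0.90 and k = 2 give 0.50 / 1.10 = 0.455 against (0.45 + 0.20) / 1.10 = 0.591.

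**Reading the tables.**
- At k = 1 there is no selection bias: the plan recovers r exactly. The gap between 0.500 and 0.550 at c = 0.90 is purely a change of estimand.
- As an estimate of the effect in visited households, the plan's ratio is too favourable to SMC if k > 1 and too unfavourable if k < 1.
- As an estimate of the cluster-wide effect, it is too favourable if k > r, equal if k = r, and too unfavourable if k < r.

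**The case against.** The strongest reply is that the two frames may differ little in practice.

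- Delivery is door-to-door, and the only description of coverage in the article is that it was high. This stands in part: near-complete coverage would make the effect small. But the statement has no percentage and concerns two other districts in 2021, so it does not settle the matter for Amudat.
- Control recruitment also filters households. A caregiver must be there to consent, Table 1 requires at least a month's residence, and Table 2 requires willingness to attend a designated health centre. This stands: many absent or mobile households drop out of control too. What matters is the difference in reach between VHT and researcher, which is why c is defined as above.
- A visit is not treatment. The child is recruited before SMC is given, so the sample is not conditioned on taking the drug. This stands, but the household is still conditioned on the visit.
- There are five monthly cycles, so a household missed at recruitment may be reached later. This stands: the all-household ratios above are then too high.
- Missed households need not show higher rates. The endpoint comes from passive surveillance, and remote or mobile children may present less often, so the recorded k may be below 1. This stands and leaves the direction open.
- The article condenses a fuller protocol, and nothing says that control children were excluded from household items or haemoglobin. This stands, so that part can only be conditional.

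A reader might infer that control children come from all households, or that the randomised comparison is broken and effectiveness overstated. The text does not support either: the control frame is not stated, and the size and sign of any bias depend on quantities that the article does not give.

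**Conclusion.** The point holds as a risk built into the recruitment rule. The article affirmatively describes two frames, and the SMC one depends on an event after allocation that control lacks. Following the text exactly gives SMC versus control a possible selection bias of unknown size and direction, and an estimand closer to the effect in reached households than to the effect of offering SMC to a cluster.

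Under the assumptions above, at 95 to 98% visited and k between 0.5 and 2, the spurious null ratio runs from 0.95 to 1.03. At 80% visited it runs from 0.83 to 1.11. With r = 0.50 and 90% visited, the plan's ratio differs from the cluster-wide one by 0 (k = 0.5), 0.05 (k = 1) or 0.14 (k = 2), if missed households never receive SMC.

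SPAQ and DP children are recruited by the same procedure, so DP versus SPAQ is untouched by this asymmetry. The baseline data matter only if control did not collect the household items and haemoglobin; in that case imbalance in them can be neither checked nor adjusted for.

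**What to change.** **As a design.** Draw households in every arm from the same listing, made before distribution and independent of VHT visits. Select one eligible child at random per household. Use the same baseline and household questionnaire and the same haemoglobin measurement in all arms, and analyse by assigned cluster.

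**For this trial**, since Study status says that data collection is complete:
1. State the household frame actually used in each arm.
2. Label the SMC-versus-control result as the effect among VHT-reached households.
3. Report the share of households visited in the trial clusters.
4. Give a sensitivity analysis over a range of coverage and of relative risk in unvisited households, with values below and above 1. A single estimate scaled by coverage is not enough, because it assumes that missed households never received SMC.
5. Adjust for baseline covariates that both arms have. Collecting missing control items afterwards is doubtful for those that change, such as migration status.

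**Cost.** A common listing and slightly longer interviews in a future round; for this trial, some reporting and analysis work. The effectiveness estimate may turn out less favourable.

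### Malaria events are linked to enrolled children only through the SMC card, and no card or other identifier is described for the control arm

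*Protocol article*

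**What the plan says.** All of this is in the protocol article. Under Recruitment and data collection (cRCT component), outcome data come from both kinds of area: "The primary endpoint will be recorded with passive surveillance conducted by study clinicians in intervention and control areas throughout the five-month study period". The way an enrolled child is recognised at a visit is then stated for the whole study population, without a split by arm: "Children recruited into the study presenting at clinics or to VHTs will be identified using information on their SMC record cards". Visit dates and RDT results supply the "time to malaria events for fitting of Cox proportional hazards regression model", and on how this is achieved the text says: "This will be facilitated through matching of codes on children's SMC cards with records of the same codes in clinic logbooks".

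The same section describes enrolment separately by arm. For controls: "In the control arm, one eligible child will be recruited at random in each household", followed by consent and a baseline questionnaire. For the others: "For the intervention arms, VHTs will be followed by a researcher as they administer SMC". Under Population, SMC eligibility in the trial district is confined to "randomly-selected areas in Amudat and Nakapiripirit". Study setting places the cRCT in Amudat.

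**The concern.** An SMC record card is, by its name, a record of receiving SMC. If the card is what turns a clinic visit into a trial event, the linkage key comes with the allocated treatment. A control child with RDT-confirmed malaria but no card code in the logbook would not show up as missing data. The child would stay in the risk set as event-free.

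That would be outcome ascertainment that differs by arm on the primary endpoint. It would act against SMC, in a study intended to inform policy on SMC outside the Sahel. Adjustment in the Cox model would not recover events that were never linked.

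**Working it through.** **Reading the passages together**

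1. Linkage key: the SMC card and its code. The section names no second identifier. The baseline questionnaire is what visit data are matched to once the child has been recognised. It is not offered as another way of recognising the child.
2. Who needs the key: every recruited child, because the endpoint is recorded in control areas too.
3. Who is described as being in contact with SMC delivery: the intervention arms only. With SMC in Amudat limited to randomly selected areas, an untreated control arm is implied, though never stated outright.
4. What control children are given at enrolment: no card or code is mentioned. The article does not say that they lack a card, and it does not say that the study issues one.

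Equal capture across arms is therefore not shown, and followed literally the written rule would not deliver it.

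**Stated figures**

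Table 1 gives 4,270 children for the cRCT, and its rows add up: 4,270 + 1,250 + 30 + 1,500 + 144 = 7,194. The article does not give the design inputs behind the 4,270, so it cannot be recomputed. That is no criticism of a condensed article, and nothing here depends on it.

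**Direction and possible size**

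Let c be the probability that a true case in an arm is linked. The observed event rate is roughly the true rate × c, so

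observed ratio ≈ true ratio × (c_SMC ÷ c_control).

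The documents give neither c nor an expected effect. Every value below is an assumption.

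| c_SMC | c_control | true ratio 0.30 | true ratio 0.50 |
|---|---|---|---|
| 1.00 | 1.00 | 0.30 | 0.50 |
| 1.00 | 0.90 | 0.33 | 0.56 |
| 1.00 | 0.75 | 0.40 | 0.67 |
| 1.00 | 0.50 | 0.60 | 1.00 |
| 0.90 | 0.70 | 0.39 | 0.64 |
| 0.90 | 0.50 | 0.54 | 0.90 |
| 0.90 | 0.30 | 0.90 | 1.50 |

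For example, 0.30 × 1.00 ÷ 0.75 = 0.40, so 70% protection would be reported as 60%. With c_SMC = 0.90 and a true ratio of 0.30, the observed ratio passes 1 only if c_control falls below 0.30 × 0.90 = 0.27. If capture is equal in the arms, at any level, the factor is 1 and the ratio is unchanged.

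The formula is approximate for a Cox hazard ratio. If some children can never be linked, the arm is a mixture of linkable and unlinkable children and hazards are no longer proportional. The direction is the same.

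**The case against.** The strongest reply is that the text does not say control children have no card. It refers to all recruited children and their cards just after stating that surveillance covers control areas, so it can be read as every enrolled child holding a coded card. Study clinicians carry out the surveillance, baseline data exist for every child, and code matching is described as an aid rather than as a condition for counting a case. Taken to its limit, a card-only rule with cardless controls would give a control arm with no events at all, which makes the benign reading more plausible. Card issue is also the kind of operational detail that a full protocol would hold.

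Much of this stands. A reader might infer that control cases were in fact missed and that the result is biased. The documents do not support that, because the absence of control cards is an inference and no linkage rates are reported. A reader might also take the illustrative ratios as estimates; they rest wholly on assumed values. Nor is there textual support for extending the problem to DP versus SPAQ, since one card procedure is described for both SMC arms.

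The reply does not remove the point. The article does not leave linkage to another document. It states a rule for the primary endpoint, names a card tied to treatment as the key, and describes an arm that appears not to receive that treatment. Study clinicians still need some means of recognising an enrolled child, and the card is the only one named.

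**Conclusion.** The point holds conditionally. As described, ascertainment of the primary endpoint relies on a card that belongs to SMC delivery, and nothing shows that it works equally well in the control arm. If control capture is lower, SMC protection against control is understated, and in an extreme case the ratio could pass 1. If all children carried the same coded card, there is no bias from this source and one sentence settles it.

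The size cannot be determined from the article. The conclusion rests on two assumptions: that the control arm receives no SMC (implied by the Population and Recruitment text), and that control children held no equivalent identifier (neither stated nor excluded). The comparison of DP with SPAQ is outside the finding provided both SMC arms held cards.

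**What to change.** By design, use one study ID as the linkage key at clinics and with VHTs. Issue it at enrolment to every child in all arms, independently of the SMC card.

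Study status reports that data collection is complete, so in practice:

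- State which identifier control children carried, and whether it was the same as in the SMC arms.
- If it was not, re-link enrolled children in all arms to the clinic and VHT registers with one common algorithm, using only identifiers held both in the baseline data and in the registers.
- Report, by arm, the number and proportion of enrolled children with at least one linked visit, and how each was linked. These are descriptive figures: SMC should itself reduce malaria visits, so a difference between arms does not by itself measure capture.
- Add a sensitivity analysis of the SMC-versus-control hazard ratio over stated assumptions about unequal capture. Do not scale the hazard ratio by the share of all RDT-positive register entries that were linked. Only one child per sampled household is enrolled, so registers will contain children who were never in the trial, and that share mixes linkage with the fraction enrolled.

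The cost is a one-off re-matching exercise, needed only if identifiers differed, plus a short addition to the report. No further participants are needed.

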**Methods:**

A Type II hybrid effectiveness-implementation study design consisting of four components: 1) a cluster randomized controlled trial (cRCT) using passive surveillance to establish confirmed malaria cases in children using both SPAQ and DP; 2a) a prospective cohort study to determine the chemoprevention efficacy of SPAQ and DP (if SPAQ or DP clears sub-patent infection and provides 28 days of protection from new infection) and whether drug concentrations and/or resistance influence the ability to clear and prevent infection; 2b) a sub study examining pharmacokinetics of DP in children between 3 to <6 months; 3) a resistance markers study in children 3–59 months in the research districts plus the standard intervention districts to measure changes in resistance marker prevalence over time and finally; 4) a process evaluation.

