### Data analysis

**
*cRCT component.*
** We will accomplish data analysis using Stata and excel. The proportion command, with 95% confidence intervals calculated using a logit transform will be used to compute coverage. Population size weights will be applied with the svy: command as appropriate for the estimates of coverage indicators whereby a self-weighting sample was not possible to achieve. The pertinent indicators will be calculated using proportions per district and an average across both districts. The confidence interval (CI) of 95% will be used to provide a range of values around the estimate within which selected result will be expected to fall.

Data from HMIS will be retrospectively analysed to identify epidemiological trends in malaria in the study districts by age group. Summary statistics will be computed and data will be graphically presented by month over the study period.

**
*Chemoprevention efficacy cohort study.*
** Relevant mutations distributions and proportions will be analysed comparing parasitological efficacy between groups of mutations. Analysis of the blood drug concentrations will be done as a cohort by mean, median and standard deviation, and statistical tests of their associations with treatment outcomes, precisely drug levels on day seven. Outliers with low levels of drug concentration based on the outcome measures described will be focused upon. Positivity on day 28 will be associated with the antimalarial drug resistance genotype. Chemoprevention failure rates will be reported on as the cumulative failure rate using Kaplan-Meier analysis of the proportion. Time to event analysis will be incorporated to assess duration of SMC protection.

**
*Resistance markers study.*
** The prevalence of Pfdhps, Pfdhfr Pfcrt and Pfmdr1 and K13 alleles will be measured in parasites obtained from smear positive children. Additionally, the copy number of Pfplm2 will also be assessed.

**
*Process evaluation component.*

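### The coverage analysis under the cRCT heading is set by district, not by randomised arm, and ties survey estimation to weighting alone; cluster handling in the Cox model needs confirming

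*Protocol article*

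**What the plan says.** All references are to the Protocol article.

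- **Design.** The abstract describes component 1 as "a cluster randomized controlled trial (cRCT) using passive surveillance to establish confirmed malaria cases in children using both SPAQ and DP".
- **Place.** Study setting: "The cRCT will be conducted in Amudat". Table 1 agrees, describing the 4,270 children as "cRCT: Sample of eligible children in Amudat district of age 3–59 months, resident in the study area for at least a month".
- **Arms and sampling.** Recruitment and data collection describes a control arm and more than one intervention arm. Households are drawn at random within selected communities, one child per household.
- **Coverage, unit of reporting.** Data analysis, cRCT component: "The pertinent indicators will be calculated using proportions per district and an average across both districts".
- **Coverage, estimation.** The same paragraph uses the proportion command with logit-transformed 95% intervals, and adds: "Population size weights will be applied with the svy: command as appropriate for the estimates of coverage indicators". The sentence goes on to limit this to cases where the sample could not be made self-weighting.
- **Coverage surveys, place.** Population: "Kotido, Moroto and Nabilatuk districts (where delivery is continuing from Phase 1 and where coverage surveys will be conducted in Phase 2".
- **Malaria events.** Recruitment and data collection says that clinic dates and RDT confirmations are recorded so as to calculate "follow-up time and time to malaria events for fitting of Cox proportional hazards regression model". The Data analysis text for the cRCT does not return to this model. After coverage it covers only descriptive trends from routine health-facility data.

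**The concern.** Two stated rules look wrong for a cluster-randomised trial in one district.

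First, the reporting unit. A per-district proportion averaged over two districts does not correspond to a trial held in one district, or to surveys held in three others. Within Amudat, a single district figure pools the control arm with the intervention arms. A reader of the results would want to know how much SMC each arm received before comparing SPAQ with DP. The stated rule does not deliver that.

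Second, the variance. Weighting and clustering are separate matters. Equal selection probabilities remove the need for weights, but children from the same community still resemble each other in whether they were reached. If survey estimation is used only when weights are needed, a self-weighting cluster sample gets a plain proportion and an interval that treats the children as independent.

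The same question arises for the Cox model, where more is at stake because it concerns the malaria endpoint. There, however, the article fixes nothing that can be called wrong.

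**Working it through.** **1. The plan's own figures.** The Table 1 total reproduces: 4,270 + 1,250 + 30 + 1,500 + 144 = 7,194. The 4,270 itself cannot be reproduced: the article gives no event rate, effect size, power, number of clusters, cluster size or ICC.

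**2. Which two districts?**

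| Possible meaning | Source | Fit with the cRCT heading |
|---|---|---|
| The trial district | Study setting; Table 1 | One district, not two |
| The coverage-survey districts | Population | Three districts, none of them Amudat |
| The two research districts, Amudat and Nakapiripirit | Recruitment, resistance markers study | Two, but Study setting gives Nakapiripirit to the efficacy cohort, not the trial |
| The two districts of the first phase, Kotido and Moroto | Study design | Two, but neither is in the trial |

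No reading fits both the heading and the stated locations. District labels vary elsewhere too. Aims and objectives counts two research and three standard districts, while Study design counts three and two. Study design has Nabilatuk receiving SMC for the first time, while Population has delivery there continuing from phase 1.

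**3. What a district figure says about arms.** Write w for the share of children in each arm and c for that arm's coverage. The Amudat figure is w_S·c_S + w_D·c_D + w_C·c_C (SPAQ, DP, control). Many different pairs (c_S, c_D) give the same total, so arm coverage cannot be recovered from it. Averaging with a second district moves it further away.

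**4. Interval width for coverage.** Design effect DE = 1 + (m − 1) × ICC, where m is children per cluster. The honest interval on the logit scale is wider by √DE. A nominal 95% interval without adjustment actually covers 1 − 2[1 − Φ(1.96/√DE)]. Neither m nor ICC is in the article, so all inputs below are assumptions.

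| m | ICC | DE | Too narrow by factor | Actual coverage of a nominal 95% interval |
|---|---|---|---|---|
| 20 | 0.02 | 1.38 | 1.17 | 90.5% |
| 20 | 0.05 | 1.95 | 1.40 | 84.0% |
| 20 | 0.10 | 2.90 | 1.70 | 75.0% |
| 50 | 0.02 | 1.98 | 1.41 | 83.6% |
| 50 | 0.05 | 3.45 | 1.86 | 70.9% |
| 50 | 0.10 | 5.90 | 2.43 | 58.0% |

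Example: m = 20, ICC 0.05 gives DE = 1 + 19 × 0.05 = 1.95 and √1.95 = 1.40.

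**5. The Cox model, conditionally.** If it were fitted with no cluster adjustment, the same formula gives a rough guide with m = 4,270/K, for K clusters in total. K and ICC are again assumptions.

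| K | m | ICC | DE | SE factor | True error of a nominal 5% test |
|---|---|---|---|---|---|
| 200 | 21.4 | 0.005 | 1.10 | 1.05 | 6.2% |
| 90 | 47.4 | 0.01 | 1.46 | 1.21 | 10.5% |
| 60 | 71.2 | 0.02 | 2.40 | 1.55 | 20.6% |
| 30 | 142.3 | 0.05 | 8.07 | 2.84 | 49% |

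These rows describe an analysis that the article does not say will be done. They show only why one sentence of confirmation is worth having.

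**The case against.** The strongest reply is that a reader might infer from the article that the primary Cox model ignores clustering, and hence that the trial's treatment comparisons will have intervals that are too narrow. The text does not support this. The model is named once, in a data-collection section, to explain why dates are kept. No arm term, covariates or variance estimator is given, and none is excluded. Shared frailty or cluster-robust variance is detail that a condensed article leaves to the full protocol or SAP. This objection stands in full, and the error rates in step 5 remain hypothetical.

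Three further replies stand in part.

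- The svy: prefix can carry cluster-based variance once a primary sampling unit (PSU) is declared, and the article does not say that none will be. That is true where svy: is used. But the stated trigger for using it is the absence of a self-weighting sample, so a self-weighting sample falls back, on a literal reading, to the plain command.
- The article nowhere says that coverage is meant to explain differences between SPAQ and DP. Agreed: it would be too strong to say the plan fails a purpose of its own. What remains is that the stated unit gives no arm-level figure and matches no stated location.
- Delivery contact is partly built into the trial sample: "For the intervention arms, VHTs will be followed by a researcher as they administer SMC", and households are drawn from those visited. That covers enrolment only. It says nothing about later cycles and is not a coverage estimate by arm.

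Finally, the unit of randomisation is nowhere stated outright. The article speaks of selected communities in one place and randomly selected areas in another, so the community is an inference.

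**Conclusion.** The point holds for the coverage analysis. The reporting unit under the cRCT heading conflicts with Study setting, Table 1 and Population, and produces no coverage by randomised arm. This rests on the text alone and needs no assumption.

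The variance rule is also badly fixed, because it links survey estimation to weighting only. Coverage intervals from a self-weighting cluster sample would be too narrow if the ICC is positive. The size cannot be computed from the article; over the assumed values in step 4 the factor runs from 1.17 to 2.43.

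For the Cox model there is no demonstrated error, only an unstated item to confirm. The consequence, intervals that are too narrow and too many false-positive findings, follows only if the model were fitted without cluster adjustment. No figure in the article is shown to be wrong.

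**What to change.** 1. Reconcile Study setting, Population, Recruitment and data collection, and Data analysis on which districts the coverage indicators refer to.
2. For the trial, report coverage by arm within Amudat, from a source that records SMC receipt. SMC record cards would serve if they log doses. The end-of-round items added to the trial questionnaire would not obviously serve: they are described as household questions, with wealth, language, migration and education as examples. Because intervention households are drawn from those already visited, label the result as receipt among enrolled children rather than population coverage.
3. Report the survey districts separately, with population weights.
4. Declare the sampling cluster as PSU for every coverage estimate, self-weighting or not.
5. Add one sentence confirming that the Cox model uses shared frailty or variance clustered on the unit of randomisation, and name that unit.

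The cost is a few lines of wording and Stata code, and somewhat wider intervals. Study status says that data collection is complete and final analysis still ahead. The wording and variance changes need no new data; coverage by arm depends on whether receipt was recorded.
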